## Abstract

**Background:**

The elderly population worldwide is increasing exponentially which will be associated with more people suffering from cognition and fitness declines. The well-established benefits of exercise training for the elderly’s cognitive and physical functioning have been observed. However, the amalgamated effect of combining cognitive and physical exercises on the older adults’ cognitive functions, physical fitness, or psycho-related health remains unclear. Thus, this study protocol was planned to conduct different combinations of cognitive and/or physical training interventions to community-dwelling older adults and expected to see the multifaceted effects of the varied combination of training on their health.

**Methods:**

This study is a cluster randomized controlled trial (CRCT). A total of 285 older adults (age ≥ 60) from twenty elderly centres as clusters will be randomly selected and assigned to intervention groups (IGs, *n* = 16) or control groups (CGs, *n* = 4). Each IG will be randomly assigned to one of the four combinations of three training modes that include cognitive (A), physical (B), and combined cognitive and physical training (CCPT, i.e. C), namely Mixed ABC, A + B, C + A, B + C. The intervention will last for 4 months in which the training is conducted for 16 sessions, 2 sessions per week, and 60 min per session. Four repeated assessments (pre-test, two post-training tests after 2 months and 4 months, and a follow-up test) will be conducted. The CG will only receive the four repeated assessments but no intervention. The outcome measures include cognitive tests (tests of execution, memory, and psych-social status), physical fitness, and dynamic balance tests.

**Discussion:**

This study will provide substantial evidence that the integrated format of cognitive and physical exercises training will have higher cognition and fitness impact than the single training modes, and all these mixed modalities will have greater positive outcomes than the control condition. If the effectiveness is proven, the intervention can be further explored and extended to the nation so that many more elderly would be benefited.

**Trial registration:**

The trial has been registered in the ClinicalTrials.gov in U.S. NIH (ID: NCT04727450, date: January 27, 2021).

**Supplementary Information:**

The online version contains supplementary material available at 10.1186/s12877-022-03031-5.

## Background

The aging population worldwide is expected to increase exponentially. The elderly population in Hong Kong is projected to have doubled in size in the coming 20 years, from 16.6% in 2016 to 31.1% in 2036 [1]. Biological aging results in cognitive and physical declines and it contributes to possible loss of functional independence and disability [2], which consequently have profound impacts on public health in terms of healthcare utilization and long-term health cost [3]. Along with the current outbreak of COVID-19, the impacts of social isolation are notable on the older population experiencing detraining and physical inactivity accompanied by a marked decline of mental well-being [4].

In the last decade, researchers have studied brain aging with experimental results revealing the brain being neuroplasticity throughout life [5] and such plasticity can be maintained with regular physical or cognitive stimulation [6]. Numerous observational studies and systematic reviews concluded that various modes of exercises including aerobic exercises, resistance training, the combination of aerobic and resistance, and mind–body exercises (e.g., tai chi, yoga, dance) [5] or cognitive training (e.g., video games, card, and board games) [7, 8], yield positive outcomes in specific cognitive domains. Several evidence has also demonstrated that physical activity can be effective in enhancing mental well-being and preventing mental disorders [9–12]. Based on these exciting pieces of evidence, it can be assumed that the combination of physical and cognitive activities might have more benefits than either intervention individually.

Some researchers have investigated the effect of combined cognitive and physical training (CCPT) using different intervention characteristics [13]. For instance, Shatil (2013) found improvement in cognitive performance in both intervention groups of cognitive training only and CCPT than the control group with 16-week training programs [14]. [name]’s research team has also conducted a pilot study entitled ‘Brain Invigoration Gross Motor Activation Program’ (BIGMAP), which was a CCPT program consisting of a set of 10 cognitive games combined with physical exercises of various difficulty levels [15]. The games and activities of BIGMAP were delivered to 466 elderly people (Mean ± SD: 73.6 ± 7.30 years) from 33 elderly centres in Hong Kong, with each training session lasting for 75 min offered twice a week. After 10 weeks’ training, significant improvements were found in both cognitive and fitness functioning as compared to that at baseline. However, a major weakness of the project was that it was not a randomized controlled trial (RCT), and did not investigate the participant’s motivation and psycho-social related measures. An RCT study is needed to test its effectiveness.

Meanwhile, another research group in Hong Kong conducted a 12-month cluster RCT study focusing on the effectiveness of four different interventions on cognition, which comprised of physical exercise, cognitive activity, CCPT, and social activity for older adults with mild cognitive impairment [16]. They found no changes in dementia stage and mild cognitive impairments tested by Clinical Dementia Rating sum of boxes scores (CDR-SOB) and Disability Assessment for Dementia-Instrumental Activities of Daily Living scores (DAD-IADL) across time and intervention groups. However, a more significant improvement of the Alzheimer’s disease assessment scale-cognitive (ADAS-Cog) subscale, which was considered the gold standard for assessing the efficacy of antidementia treatments, has been observed by post-hoc subgroup analyses after the 12-month CCPT, as compared with the other interventions [16]. A systematic review conducted by Rahe and Kalbe (2015) summarized the findings of four RCTs and four non-RCTs related to the benefits of CCPT on cognition, in which only three out of the four none-RCT studies showed the superiority of combined training when compared to single interventions while all the four RCT studies failed to show any benefit of CCPT [17]. Similarly, the authors in a recent meta-analysis on this research area stated that although the CCPT showed advantage compared to a single intervention, the data is far from being conclusive due to the heterogeneity of studies or too few studies examining the combination effect [18, 19], hence, additional investigation is necessary. Also, according to another two review studies summarizing the possible benefits of CCPT [13, 18], there was a need to determine the effectiveness of CCPT vs. cognitive training only (based on board games) vs. physical training on the cognitive functions, physical fitness, psychosocial measures (i.e. loneliness) of community-dwelling older adults.

### Research objectives and hypothesis

The purpose of this study is twofold: first, to determine the effectiveness of four mixed modalities, namely Mixed ABC, A + B, C + A, and B + C, of three training programs (A: cognitive training, B: physical training, and C: combined cognitive and physical training (CCPT)) on cognition, fitness, and psychosocial-related health of community-dwelling older adults in Hong Kong; and second, to determine which specific training program being most effective among the three programs as compared to the control group (CG).

The hypothesis is that participants with the integrated format of three training modes will have higher cognition and fitness scores than the participants with the other combinations of two training modes, and all these mixed modalities will show greater positive outcomes than the control group.

## Methods

### Research design

This study is a cluster randomized controlled trial (CRCT), to be carried out in 20 community elderly centres (see Fig. 1). The elderly centres will be randomly selected from the population list of elderly service providers in the 18 districts of Hong Kong and assigned to either one of the 4 Intervention Groups (IGs) or the Control Group (CG). There will be 16 centres in the IGs and 4 centres in the CG participating in a 6-months program (4-month intervention with 2-month follow-up). The 20 participating centres will be equally allocated to two Phases, I and II, with each Phase involving 8 centres in IGs and 2 centres in CG. Each IG will be randomly assigned to one of the four combinations of three training modes that include cognitive (A), physical (B), and combined cognitive and physical training (CCPT, i.e. C), namely Mixed ABC, A + B, C + A, B + C. The intervention will last for 4 months in which the training is conducted for 16 sessions, 2 sessions per week, and 60 min per session.

**Fig. 1 Fig1:**
[figure not shown]
Flow diagram of the study through two phases of the CRCT, including recruitment, allocation, intervention, and data collections points

In each phase, four repeated assessments (T1-T4) will be conducted: T1 is the pre-test before intervention; T2 and T3 will be conducted on intervention right after the end of 2-month and 4-month, respectively; T4 is a follow-up test conducted 2 months after the completion of all intervention training. Participants of CG will be asked to assume regular-daily habitual activities and take four repeated assessments only.

The study is designed in accordance with the SPIRIT (Standard Protocol Items: Recommendations for Interventional Trials). The study protocol has been approved by University Research Ethics Committee (REC/19–20/0066) and registered at ClinicalTrials.gov Identifier: NCT04727450.

### Sample size

As suggested by Brown et al. (2015) [20], the first step of CRCT sample size estimation is to determine one for a non-clustered design. Based on the repeated measures of ANOVA analyses of 4 trials by 5 groupings (4 IGs + 1 CG) with parameters set to an effect size of 0.175 (small to medium), an alpha level of 0.05, power of 0.90, rho of 0.5, the sample size (*n*_*n*_) estimated is 95 (calculated by G*Power software). Next, the second step is to determine the design effect (*D*_*e*_) for clustering estimation. It is calculated with a group size of 15 and ICC of 0.1 (from previous a study titled BIGMAP, to be published) [15] and yields 2.4. The required sample size for a CRCT is 228 (i.e., *n*_*n*_×*D*_*e*_). By considering a 20% of attrition rate of the participants, the total sample size (*N*) of this study is set at 285, composed of 20 groups/centres of 14–15 participants each.

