### Statistical analysis plan

Data analysis will be performed using the Statistical Package for social sciences (IBM SPSS ver. 27). All data points that were considered outliers, which are out of the interquartile range (IQR) covering the 50% central of samples, will be excluded from analyses. For analyzing program effects, a mixed-effects ANOVA will be used. In this model, there will be a between-subjects factor consisting of five groups (CGs = 0, IGs = 1 to 4) and a within-subject factor consisting of four Trials (Time = 1 to 4). The dependent variables will be the outcome measures of the three cognitive tests and the five physical fitness tests. The independent variables will be time (1 pre-test, 2 post-tests, and 1 follow-up) and intervention (IGs with 4 combinations of training modes & CGs). The participating elderly centre as a cluster will be treated as a random effect. Assumptions (normality, sphericity, etc.) for mixed-effects ANOVA will be tested using an alpha level set as 0.05. The focus of this mixed-effects ANOVA will be mainly on the between-group differences, i.e., the differences among the four IGs. Post-hoc comparisons among IGs will be conducted with Bonferroni correction after finding significant effects. Next, for analyzing specific intervention effects in the 3 treatments crossover design, a similar mixed-effects ANOVA will be used. In this second model, there will be one within-subject factor of four repeated trials (Time = 1 to 4). The dependent variables will be the outcome measures of the three cognitive tests and the four physical fitness tests. The independent variables of time (pre-test, 2 post-tests, and follow-up) and three training modes will be examined by ANOVA with repeated measures. The focus of the second model is to examine the individual effect of the three training modes, so a pre-planned contrast will be conducted to examine their effects. Based on these statistical analyses, results and conclusions will be drawn.

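### The stated power of 0.90 at n = 95 belongs to the group-by-time interaction, not to the between-group comparison that the analysis section names as its focus

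*Protocol article*

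**What the plan says.** The Sample size section of the protocol article starts from a non-clustered calculation for "repeated measures of ANOVA analyses of 4 trials by 5 groupings (4 IGs + 1 CG"), with "an effect size of 0.175 (small to medium"). At "an alpha level of 0.05, power of 0.90, rho of 0.5, the sample size" is 95, "calculated by G*Power software". The section does not say whether the test is the between-subjects effect, the within-subjects effect or their interaction. It then applies a design effect from "a group size of 15 and ICC of 0.1", which gives 2.4. It states that "The required sample size for a CRCT is 228" and inflates this to 285 for 20% attrition.

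The Statistical analysis plan section describes a mixed-effects ANOVA with a five-level between-subjects factor, a four-level time factor and centre as a random effect. It adds: "The focus of this mixed-effects ANOVA will be mainly on the between-group differences, i.e., the differences among the four IGs". Bonferroni comparisons among the intervention groups (IGs) follow if effects are significant. The interaction of group with time is not named anywhere in that section.

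**The concern.** A repeated-measures ANOVA with these two factors has three omnibus tests, and the same f, rho and n give them very different power. The article quotes one power figure without naming its test, and elsewhere names a test of interest. A reader will put the two together and take 90% as the power for differences among the training combinations. If the figure was computed for another effect, that reading is wrong, and the article's main hypothesis (that the three-mode programme does better than the two-mode ones) would rest on a power statement that does not cover it.

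The choice of test also matters apart from power. The between-subjects main effect averages over all four assessments, including the pre-test, where randomised groups are expected to be alike. The interaction looks at differences in change.

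**Working it through.** **Inputs.** From Sample size: f = 0.175 (f² = 0.030625), m = 4 assessments, k = 5 groups, rho = 0.5, alpha = 0.05, N = 95, cluster size 15, ICC 0.1, attrition 20%. From Research design: 20 centres, of which 16 are in the IGs. Assumption: sphericity holds (epsilon = 1, the G*Power default). Power is from the noncentral F distribution.

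**1. Reproducing 95.**

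- *Interaction:* λ = f²Nm/(1 − rho) = 0.030625 × 95 × 4 / 0.5 = 23.3, with df 12 and (95 − 5) × 3 = 270. Power is 0.909. At N = 90 it is 0.889, so 95 (19 per group) is the smallest balanced size that reaches 0.90.
- *Within (time):* same λ, df 3 and 270. Power at 95 is 0.988, and 60 would be enough.
- *Between (group):* λ = f²Nm/(1 + (m − 1)rho) = 0.030625 × 95 × 4 / 2.5 = 4.66, with df 4 and 90. Power is 0.352. Power is 0.896 at 315 and 0.901 at 320, so 320 would be needed.
- *G*Power's alternative SPSS-style effect-size scaling:* 250 for the interaction, 515 for between.

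Only the default interaction gives 95. The later steps also reproduce: 1 + 14 × 0.1 = 2.4; 95 × 2.4 = 228; 228 / 0.8 = 285.

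**2. The between-subjects test with f = 0.175 entered for it.** By the plan's own design effect, 228 clustered participants are worth 95 independent ones, so the final sample size does not alter this comparison.

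| Test | λ | df | Power |
|---|---|---|---|
| Five groups, N = 95 | 4.66 | 4, 90 | 0.35 |
| Five groups, centre-level df (20 − 5) | 4.66 | 4, 15 | 0.28 |
| Four IGs, N = 76 (4/5 of 95) | 3.72 | 3, 72 | 0.32 |
| Four IGs, centre-level df (16 − 4) | 3.72 | 3, 12 | 0.25 |

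Varying rho from 0.3 to 0.8 moves the five-group figure (df 4, 90) from 0.46 to 0.26.

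**3. The between-subjects test if the planned effect is the interaction at f = 0.175.** One f in two tests is not one clinical effect. Assume that groups are equal at T1 and that their differences follow a common time profile c over T1 to T4. The between-group f is then 0.175 × mean(c)/SD(c). For c = (0, 1, 1, 1), the mean is 0.75 and the variance 0.1875, the ratio is 1.732, f = 0.303, and λ = 0.303² × 95 × 4 / 2.5 = 13.97. The other profiles follow in the same way:

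| Profile T1–T4 | Implied between f | Power, df 4, 90 | Power, df 4, 15 |
|---|---|---|---|
| Sustained from T2 (0, 1, 1, 1) | 0.303 | 0.84 | 0.73 |
| Growing, then held (0, 1, 2, 2) | 0.264 | 0.72 | 0.59 |
| Partly fading (0, 1, 2, 1) | 0.247 | 0.65 | 0.53 |
| Gone by T4 (0, 1, 2, 0) | 0.158 | 0.29 | 0.23 |

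**4. The interaction with centre-level df.** With df 12 and 3 × 15 = 45, λ = 23.3 gives power 0.84. If 228 are analysed, there are 228/20 = 11.4 per centre, the design effect is 1 + 10.4 × 0.1 = 2.04, the effective n is 228/2.04 = 111.8, λ = 27.4, and power is 0.90. Without the sphericity assumption, power at N = 95 and 270 df falls from 0.909 to 0.88, 0.83 and 0.70 at epsilon 0.9, 0.75 and 0.5.

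**The case against.** The best defence is that the analysis section is loosely worded and the sample size is sound. It speaks of between-group differences, not of a group main effect, and in a trial with a pre-test that phrase can mean differences in change, which is the interaction. The sentence may also serve only to separate this model from the second one, which looks at the individual training modes. On that reading the calculation and the analysis agree and one clarifying phrase is enough. This stands as a possibility, and it limits the severity. It does not remove the point: the section presents group as the between-subjects factor and never mentions the interaction, and the Sample size section does not name its test either. The interaction has to be inferred by reproducing 95.

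The second objection concerns size. A reader might infer that the featured test has power of about 0.3 for the planned effect and would miss it about two times in three. The documents do not support that. The value near 0.3 comes from carrying f = 0.175 unchanged from one effect to another. If the planned effect is the interaction, the main-effect power depends on the time profile and is that low, among the profiles examined, only when the benefit has vanished by T4. Nor does any part of the article plan to read a null result as equivalence, so that consequence cannot be attributed to it. No pairwise effect size is given, so no power for a single pair of IGs can be derived from the article.

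Third, the numbers 95, 2.4, 228 and 285 are all correct as arithmetic. That is so; the fault is in which test the 0.90 is attached to.

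**Conclusion.** The point holds as a mismatch between two sections and should be fixed. The stated 0.90 is the power of the omnibus group-by-time interaction. It is not the power of the between-subjects comparison that the analysis section features when read literally. That comparison has power 0.35 or 0.32 (0.28 or 0.25 with centre-level df) if f = 0.175 is meant for it. If f = 0.175 is the interaction and groups are equal at T1, power is about 0.29 to 0.84 (0.23 to 0.73 with 15 df). It is below 0.90 in every profile examined. These ranges rest on rho = 0.5, the plan's design effect and the assumed profiles.

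The interaction itself is powered roughly as claimed, about 0.84 to 0.90 with centre-level df under sphericity. The trial's size is therefore not shown to be wrong for that test.

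**What to change.** In Sample size, state that 0.90 refers to the omnibus group-by-time interaction, and give about 0.84 to 0.90 as its power with centre-level degrees of freedom. In the Statistical analysis plan section, make that interaction, or group contrasts adjusted for the T1 value, the primary test in place of the between-subjects main effect. If T1-adjusted contrasts are chosen, they need their own power statement.

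Do not claim 90% power for the between-group main effect or for the Bonferroni comparisons among IGs. If power for these is reported, state the assumed effect (for the main effect, also the time profile) and use centre-level degrees of freedom.

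The change is to text only and needs no extra recruitment. Its cost is a less favourable power statement for the main effect and the pairwise comparisons.

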### Participants recruitment

Eligible elderly participants (age 60 or above) who have passed a cognitive and emotional screening test will be recruited by the community centres with preset inclusion and exclusion criteria. The demographic information of all participants will be collected in terms of age, educational level, medical history, living conditions, occupation, and daily activity patterns. All participants will be informed of the objectives, potential risks, benefits and the data collection procedure of the study. They will sign a written consent prior to their participation.

The inclusion criteria of participants include willingness and capability to give informed consent to participate in the training and testing of this study; and pass the cut-off of the screening tests (cognitive and emotional): Montreal Cognitive Assessment Test (MoCA), a widely used assessment test for cognition [21], with the score above 19 (satisfactory basic function). The elderly will be excluded if s/he has a history of systematic cardiovascular diseases causing cognitive impairments, poorly controlled hypertension, stroke, Parkinson’s disease, early stages of Alzheimer’s disease, brain injury or brain operations, and other complicated conditions that could have prevented attending regular attendance and taking assessments in the elderly centre; concurrent major psychiatric disorder (e.g. major depressive disorder, schizophrenia) or drug and alcohol abuse; and currently receiving regular physical (perform aerobic, flexibility, and stretching exercises for 3 days per week, 45 min per session, for 1 year or longer) and cognitive exercises (such as playing mahjong, chess, bridge, and reading for more than 30 min per session and 3 times per week, for 1 year or longer).

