### Interventions

Each selected elderly centre will be randomly assigned to either IGs or CG and asked to help to recruit participants with a sample size of 14–15 older adults. There will be 16 centres in the IGs to receive four combinations of three training modes (A: cognitive training only, B: physical training only, C: CCPT) and with 4 centres in IGs. The four types of combinations are 1. Mixed ABC, 2. A + B, 3. B + C, 4. C + A, matched with 4 CGs in total. For the case of combination 1. Mixed ABC, participants will receive different training modes every 2 consecutive weeks with randomized order. For the case of combinations 2, 3, and 4, the participants’ centres will receive an assigned sequential order of two training modes with each mode lasting for 2 months. All participants of IGs will attend training sessions twice a week, and 60 min duration per session (per mode). The random allocation sequence of intervention was generated by a blinded statistician external to the research team. Due to the nature of each intervention, blinding cannot be applied to the participants, while the blinded group allocation will be applied to the data assessors and analysts. Each subject will be identified by the number code. Data from those participants having more than 70% attendance will be analyzed. No further follow-up with missing cases will be done because they will be usually missing at random (such as absences due to doctor’s appointments or being sick).

The three training modes (A, B, and C) are introduced as follows:A: Cognitive training only

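### The first (between-group) model omits age and education, which are collected, with only four centres per arm: a minor loss of efficiency and robustness

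*Protocol article*

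**What the plan says.** In the Protocol article, Participants recruitment, demographic information on all participants "will be collected in terms of age, educational level, medical history, living conditions, occupation, and daily activity patterns". Entry is from age 60, with no upper limit given.

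The Statistical analysis plan section describes the first model as a five-level group factor and a four-level time factor. It then lists the predictors: "The independent variables will be time (1 pre-test, 2 post-tests, and 1 follow-up) and intervention". It adds: "The participating elderly centre as a cluster will be treated as a random effect". No covariate is named. On the target it says: "The focus of this mixed-effects ANOVA will be mainly on the between-group differences", explained as the differences among the four intervention combinations.

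On the number of clusters, Research design says: "There will be 16 centres in the IGs and 4 centres in the CG". With four combinations this is four centres per arm, assuming an equal split. The only balancing described is the equal division of centres over two phases. On recruitment, the Interventions section says that each selected centre "will be randomly assigned to either IGs or CG and asked to help to recruit participants".

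**The concern.** WCST errors, CTT times in seconds and the fitness tests can reasonably be expected to vary with age and, for the cognitive tests, with schooling. That is an assumption; the documents do not say so. Randomising four centres per arm does little to balance such characteristics, and no stratification or matching on them is described. If centres know their assignment when they recruit, as the wording suggests, selective imbalance can be added to chance imbalance.

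In a comparison of outcome levels between arms, an imbalance in a prognostic covariate shifts the estimated difference. The variation that the covariate would explain also stays in the centre and participant variance, and so in the standard error. Both could be reduced with data the trial already plans to collect. At stake are some precision and some protection against imbalance, not the validity of the randomised comparison.

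**Working it through.** **1. The plan's own figure, and the contrast it rests on.** Inputs from Sample size: effect size f = 0.175, alpha 0.05, power 0.90, rho = 0.5, k = 5 groups, m = 4 assessments. For the group-by-time interaction the noncentrality is f² × N × m / (1 − rho), with (k − 1)(m − 1) and (N − k)(m − 1) degrees of freedom. At N = 95:
- noncentrality = 0.030625 × 95 × 4 / 0.5 = 23.275, with 12 and 270 df; power = 0.909.
- The smallest N is 93, or 95 for equal groups.
- Design effect = 1 + (15 − 1) × 0.1 = 2.4; 95 × 2.4 = 228; 228 / 0.8 = 285.

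The stated figures reproduce. The within-factor test would need 60 and the between-factor test 320, so only the interaction gives 95. No covariate enters the calculation.

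**2. Chance imbalance between two arms.** Participants per centre: 285 / 20 = 14.25. For a covariate with centre ICC r (assumed), in covariate SD units, the SD of the difference between two arms of four centres is √[2 × (r + (1 − r)/14.25) / 4].

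| r (assumed) | SD of arm difference | Chance that two given arms differ by more than 0.25 SD |
|---|---|---|
| 0 | 0.19 | 18% |
| 0.05 | 0.24 | 30% |
| 0.1 | 0.29 | 38% |
| 0.2 | 0.36 | 49% |

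These are imbalances in the covariate, not biases in the treatment effect, and they exclude selective recruitment.

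**3. Gain for an arm difference in level at one visit.** Outcome ICC 0.1 (Sample size), total SD 1. Unadjusted SE = √[2 × (0.1 + 0.9/14.25) / 4] = √0.0816 = 0.286. If the covariates explain a share R² at both levels, the variance is multiplied by 1 − R²:

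| R² (assumed) | SE | Variance reduction | Narrowing of the interval, 1 − √(1 − R²) |
|---|---|---|---|
| 10% | 0.271 | 10% | 5% |
| 20% | 0.255 | 20% | 11% |
| 30% | 0.239 | 30% | 16% |

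With 228 / 20 = 11.4 completers per centre the unadjusted SE is 0.299, and the percentage reductions are the same.

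**4. Group-by-time contrasts.** T1 is one of the four time levels. A baseline covariate with a constant effect over time adds the same amount to each of a participant's four scores and cancels from any difference between visits. One complete simulated data set (20 centres of 14, covariate explaining 20% of variance at both levels) confirmed this. The interaction estimate was 0.271 with SE 0.183, with and without the covariate. In the same data set one arm difference in level moved from −0.153 to −0.321 and its SE fell only from 0.303 to 0.300. One data set does not estimate the average gain, but it shows that the realised gain can be well below the table above.

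**5. If the T1 score is also adjusted for.** T1 has correlation 0.5 with the later score and explains 25%, leaving 0.75. A covariate with correlation q to the outcome at both visits adds 0.25q²/(1 − q²). For q = 0.3 this is 0.0247, and 0.0247/0.75 = 3%. For q = 0.5 it is 0.0833, and 0.0833/0.75 = 11%. These q values correspond to 9% and 25% of variance explained without T1.

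**The case against.** **Covariates may be left to a fuller plan.** A journal article condenses, and baseline covariates are often named elsewhere. But this section lists the independent variables, so the model is stated without covariates and not left open. If a fuller plan already names them, the point falls away.

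**The effect behind the sample size gains nothing.** This stands for complete data and a constant covariate effect. The gain is confined to arm differences in level. The plan's emphasis on between-group differences allows that reading but does not compel it. Data are unlikely to be complete, since the plan allows for 20% attrition. Conditioning on age and education may then make the missing-at-random assumption more plausible, but it would not cure selection by attendance.

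**Centre is already a random effect.** This also stands. Chance differences between centres are reflected in the standard error, so chance imbalance costs precision and does not invalidate the test. Selective recruitment is a separate problem, which two covariates would not resolve.

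**Stronger readings.** A reader might infer that both models need these covariates. The second model is described with time as its one within-subject factor and targets the individual training modes; for within-person contrasts the additive terms again cancel in complete data.

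A reader might also expect a much larger gain. If half the between-centre and 20% of the within-centre variance were explained, the ratio would be (0.05 + 0.72/11.4)/(0.1 + 0.9/11.4) = 0.113/0.179 = 0.63, a 37% reduction. The documents give no R² to support this, and it would not survive adjustment for T1. Nor is a gain established for every outcome: the RBMT is converted to scaled scores and an index, and whether these are already normed for age is not stated.

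**Conclusion.** The point holds as a minor improvement in efficiency and robustness of the first model. The plan fixes that model without two covariates it collects, in a design with four centres per arm and recruitment worded as following assignment.

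The benefit applies to between-arm differences in level: about 10-30% of the variance of a single-visit contrast, if age and education explain 10-30% of the variance at both levels. That range is assumed. The benefit is nil for complete-data group-by-time contrasts with a constant covariate effect, and about 3-11% of residual variance once the T1 score is adjusted for (correlations 0.3-0.5 assumed).

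A reader might infer that the randomised comparison is invalid or that the 285 is wrong. Neither follows: the 285 reproduces exactly, and the omission does not undermine the randomisation.

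**What to change.** In the Statistical analysis plan section, pre-specify baseline age and educational level as fixed covariates in the first (between-group) model. State their form in advance, for example age in years and the educational categories as recorded, so that covariates are not chosen after imbalances have been seen.

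State also whether the T1 score is to be a covariate. If so, remove T1 from the outcome vector and model T2-T4 only, because the same measurement cannot serve as both outcome and covariate. Leave the second model as it is on this point.

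The cost is a change of wording and a few model parameters, with no new data. As participant-level covariates they take little from the roughly 15 centre-level degrees of freedom (20 centres − 5 arms). The downside is that the gain may be small and depends on assumptions the documents cannot confirm.
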